## Abstract

**Introduction:**

Pregnancy increases the risk of periodontitis due to the increase in progesterone and estrogen. Moreover, periodontitis during pregnancy is associated with development of pregnancy and birth related complications. The aim of this study is to determine, whether periodontal treatment during pregnancy can reduce systemic inflammation and lower the risk of adverse pregnancy and birth related outcomes.

**Methods and analysis:**

The PROBE study is a non-randomized controlled intervention study conducted among 600 pregnant women with periodontitis. The women will be recruited among all pregnant women at two Danish hospitals in Region Zealand during their nuchal translucency scan and will subsequently be screened for periodontitis. The intervention group includes 300 pregnant women, who will be offered state-of-the-art periodontal treatment during pregnancy. The control group includes additional 300 pregnant women, who will be offered periodontal treatment after giving birth. Outcome measures include periodontal measures, inflammatory, hormonal and glycaemic markers as well as the prevalence of preterm birth risk, low birth weight and risk markers of gestational diabetes mellitus (GDM) and preeclampsia that will be collected from all screened women and further during pregnancy week 20 and pregnancy week 35 for women enrolled in the intervention.

**Ethics and dissemination:**

The study’s findings will be published in peer reviewed journals and disseminated at national and international conferences and through social media. The PROBE study is designed to provide important new knowledge as to whether periodontal treatment during pregnancy can reduce the prevalence of complications related to pregnancy and birth.

**Clinical trials registration:**

The study was registered on clinicaltrials.gov (NCT06110143).

## Introduction

Periodontitis is one of the most common chronic inflammatory oral conditions affecting approximately 40–70% of the global adult population [1, 2]. Periodontitis manifests in the tooth-supporting tissues and will lead to recession of gums, tooth loosening and ultimately tooth loss if left untreated [3–5]. Accumulation of plaque (biofilm) on tooth surfaces induces gingivitis, which is still reversible although the gums can become swollen, red and may bleed. In some individuals, gingivitis progresses, and the accompanying inflammation can lead to clinical attachment loss, bone resorption and loosening of teeth, which is irreversible and also marks the onset of periodontitis. If untreated, periodontitis may also result in several complications including impaired masticatory function, reduced self-esteem and reduced interest in social interactions [6]. Accumulating evidence has linked periodontitis to a wide range of common medical conditions such as diabetes, cardiovascular disease, rheumatoid arthritis and Alzheimer’s disease [7].

Pregnant women are susceptible to develop periodontitis due to hormonal and immunological changes related to the pregnancy status [8]. The immunologic changes have recently been revealed as mediators of a pathogenic shift in the oral microbiome emerging during pregnancy [9]. Studies have linked low-grade inflammation to periodontitis, also during pregnancy, by an increased vascular permeability, skewed immune responses and a shift in the composition of the periodontal microbiota [10]. Consequently, maternal periodontitis may influence offspring health through several mechanisms, including the exposure to increased inflammatory load, and creating of a dysbiosis of intrauterine microenvironment and epigenomic changes in the offspring [11, 12]. Emerging evidence, including results from a systematic review, has shown that periodontitis during pregnancy can increase the risk of premature birth (< 37 weeks gestation) and low birthweight (< 2.5 kg) [13, 14]. Studies suggest that treatment during pregnancy might reduce the risk of preterm birth, low birthweight and potentially reduce the risk of both pre-eclampsia and gestational disease [15, 16] However, studies are still debating the exact effects [17], and the biological mechanisms linking periodontitis to adverse pregnancy outcomes are not yet fully understood [18].

The prevalence of periodontitis during pregnancy has not been systematically assessed in many countries, including Denmark, and the prevalence of periodontitis from the few existing studies vary significantly with a range from 12% [19, 20] to 61% [21]. The large variation might, partly, be attributed to diverse definitions of periodontitis [22]. Still, optimal oral health care during pregnancy is often neglected, and data from the Danish Dental Association indicate that as many as 40% of Danish women in childbearing age do not visit a dentist regularly [20].

Treatment of periodontitis in pregnant women has previously been found to be safe and to have beneficial effects beyond the oral cavity for both the mother and the child [17]. Reducing complications, like gestational diabetes and preeclampsia during pregnancy, and fetal growth restriction are expected to beneficially influence the risk of later development of metabolic disturbances in the offspring [23–26]. Another advantage of treating periodontitis during pregnancy is the potential long-term reduction in risk of other chronic diseases such as diabetes, cardiovascular disease and Alzheimer’s [27].

If the findings from the PROBE study show an effect of periodontal treatment on the risk of pregnancy and birth related outcomes, the main message will be that oral hygiene, regular visits to a dentist and treatment of existing periodontitis during pregnancy should be given higher priority. Some countries, like the UK and Brazil, acknowledging the importance of good oral hygiene during pregnancy, currently offer free dental care during pregnancy. In Denmark dental care and treatment is public financed and currently free of charge for children up to the age of 21 years. Hereafter, only partly (around 40% reimbursement) subsidised. A recent study [28] on the financial consequences of providing free dental care to pregnant women suggests that the long-term beneficial effects both for the women and the offspring may be significant and justify the costs of providing treatment without patient out of pocket costs. The PROBE study plans to assess this aspect through an economic analysis. This analysis will quantify the cost-effectiveness of the preventive intervention in the PROBE study using analyses suggested by Cookson et al. 2017 [29].

### The overall rational and aim of the PROBE intervention study is

To determine the effects of the periodontal treatment intervention on a) the risk of preterm birth, low birthweight and markers of preeclampsia and gestational diabetes; and on b) changes in markers of systemic inflammation related to periodontal treatment during and after pregnancy.

## Materials and methods

### Design

Approval was granted by the Committees on Health Research Ethics in the Capital Region of Denmark (journal number H-20083249) on May 19, 2021 and by the Danish Data Protection Agency. The study will be conducted in accordance with the Helsinki Declaration and guidelines for Good Clinical Practice. The study was registered on clinicaltrials.gov (NCT06110143). The PROBE study is a controlled intervention study, where approximately 1200 pregnant women are recruited from Holbaek Hospital and Nykoebing Falster Hospital in Region Zealand in Denmark. About half of the participants are expected to have periodontitis, based on findings from other Nordic countries (1). The recruitment will take place in relation to their appointment for the nuchal translucency scan in gestational week 11–14 followed by a periodontal screening visit with a licensed dentist. The secretaries orally inform all pregnant women attending the nuchal translucency scan about the study. The pregnant women who participate will give informed written consent. Inclusion criteria for the intervention are pregnant women, who speak and understand Danish and are scheduled to give birth and either Holbaek Hospital or Nykoebing Falster Hospital, and are diagnosed with periodontitis (stage I-III) by the study dentist. Exclusion criteria are pregnant women without periodontitis, pregnant women with less than 20 healthy teeth, pregnant women with periodontitis who receives periodontal treatment and pregnant women with periodontitis stage IV.

Data from the Danish Dental Association (2019) indicate that approximately 35% of Danish women (18–39 years) with regular dentist visits have periodontitis. In the same age group, an estimated 65% of the women living in Region Zealand have regular dentist visits. There is no information about periodontitis for those 35%, who do not visit a dentist regularly. Recruitment of pregnant women with periodontitis into the study will last over a period of 18 months for the intervention group and an additional 18 months for the control group. Over a period of 18 month, we expect that approximately 600 pregnant women in the region are eligible for inclusion. Provided half of the invited women accepts the invitation to participate we can include 300 women in each of the two study arms.

The intervention group receives state-of-the-art periodontal treatment during pregnancy, and the control group receives periodontal treatment after giving birth. The method and data collection activities are the same for both the intervention and the control group, except for the timing of the periodontal treatments that are performed during pregnancy for the intervention group and after giving birth for the control group (Fig 1). The periodontal treatment will be up to approximately 20 weeks for both groups: Each included woman can receive up to five periodontal treatments.

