### Periodontal measures

The same study dentist will be performing all the periodontal examinations. Periodontal clinical parameters used to make the periodontal diagnosis are ‘plaque index’ (PI), ‘bleeding on probing (BOP)’, ‘periodontal pocket depth (PPD)’ and ‘clinical attachment loss (CAL)’ and will be measured at baseline (gestational week 11–20), and at gestational week 35–36 in the intervention group. PI will be measured during treatment (up to four treatment sessions before gestational week 35).

PI will be calculated as the mean of the amount of dental plaque present on each tooth. BOP will be calculated as the mean gingival bleeding observed 10 seconds after probing and will be recorded as a percentage. CAL will be measured (in ‘mm’) as the distance from the cemento-enamel junction to the base of the gingival sulcus [30]. PPD will be measured (in mm) as the distance from the gingival margin to the base of the gingival sulcus [30].

As per the clinical definition of periodontitis, a patient will be diagnosed with periodontitis, if a CAL of at least 1 mm is observed on at least two non-adjacent teeth, or a facial/ lingual CAL of at least 3mm is observed on at least two teeth (which may be adjacent) [31]. The observed CAL must not be due to reasons other than periodontitis e.g., traumatic gingival recessions, cervical dental caries, endodontic lesion draining through the marginal periodontium, vertical root fracture or complications associated with the second molar [31]. Periodontitis will further be classified into stages as per the severity of the disease, defined by the worst affected tooth with the highest observed CAL. Due to the lack of radiological diagnosis, CAL, PPD and number of missing teeth, will be the diagnostic criteria for staging periodontitis: StageⅠ(CAL = 1–2 mm, PPD ≤ 4 mm, no missing teeth), StageⅡ (CAL = 3–4 mm, PPD ≤ 5 mm, no missing teeth), Stage Ⅲ (CAL ≥ 5 mm, PPD ≥ 6 mm, 1–4 missing teeth) and Stage Ⅳ (CAL ≥ 5 mm, PPD ≥ 6 mm, ≥ 5 missing teeth) [31].

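### Arm follows recruitment period, so acceptance and diagnosis can depend on it, and the adjustment list omits dental attendance and baseline periodontal severity

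*Protocol article*

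**What the plan says.** The abstract (Methods and analysis) declares the design openly: "The PROBE study is a non-randomized controlled intervention study conducted among 600 pregnant women with periodontitis". Design states that recruitment "will last over a period of 18 months for the intervention group and an additional 18 months for the control group", which reads as two separate periods, so the date of recruitment fixes the arm. The abstract gives the control offer: "The control group includes additional 300 pregnant women, who will be offered periodontal treatment after giving birth".

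Design also gives the order of steps. "The secretaries orally inform all pregnant women attending the nuchal translucency scan about the study", at the "nuchal translucency scan in gestational week 11–14 followed by a periodontal screening visit with a licensed dentist". Inclusion then requires a stage I–III diagnosis by the study dentist. The expected yield uses a single acceptance figure: "Provided half of the invited women accepts the invitation to participate we can include 300 women in each of the two study arms".

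Periodontal measures states: "The same study dentist will be performing all the periodontal examinations". A case can rest on 1 mm of attachment loss on two non-adjacent teeth, and staging is done without radiographs. The only blinding described is that of the cytokine assay operators (Analyses of blood samples).

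Statistics plans an intention-to-treat analysis and a regression adjusted for age, BMI, parity, smoking, medicine use, socioeconomic status and education. Dental attendance and baseline periodontal severity are not on that list. The baseline questionnaire covers oral health care and dental habits (Design), and the periodontal parameters are measured at baseline (Periodontal measures).

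**The concern.** Two steps stand between the scan and the analysis: the woman accepts, and the dentist diagnoses. Both come after the calendar has settled the arm.

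- **Acceptance.** One period offers treatment during pregnancy and the other offers it after birth. If the offer is described at invitation, the two may appeal to different women.
- **Diagnosis.** A low attachment-loss threshold is applied by an examiner who knows which period it is.

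This differs from ordinary calendar-time change. It could arise even if nothing in the population or in obstetric care changed over the 36 months. Intention-to-treat protects the comparison only from inclusion onwards. Covariate adjustment can help, but the two variables closest to the selection mechanism are not in the model. At stake is whether a difference in gestational length or birth weight can be read as an effect of treatment.

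**Working it through.** **Order of steps against knowledge of arm**

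| Step | Who decides | Arm predictable? |
|---|---|---|
| Information at the scan | Secretaries | Yes, from the date |
| Acceptance | The woman | Probably, through the offer; not stated |
| Stage I–III diagnosis | Study dentist | Yes, from the date |
| Birth weight, gestational length | Not assessed by the dentist | Not a dentist judgement |

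The article describes no step that conceals the arm in the first three rows.

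**Reproducing Table 1**

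Inputs from Power calculation: SD 567 g and 9 days, 80% power, alpha 0.05 (taken as two-sided), equal arms.

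Detectable difference = (1.960 + 0.842) × SD × √(2/n per arm).

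- Birth weight, 300 per arm: SE = 567 × √(2/300) = 46.3 g, giving 129.7 g (stated 130).
- Birth weight, 200 per arm: SE = 567 × √(2/200) = 56.7 g, giving 158.9 g (stated 159).
- Gestational length: 2.06 and 2.52 days (stated 2.1 and 2.5).

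Table 1 is correct.

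**What an entry difference would do**

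Let b be a difference between arms that selection causes and the regression leaves in place. With no treatment effect, the chance of p < 0.05 is

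1 − Φ(1.96 − b/SE) + Φ(−1.96 − b/SE).

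The documents give no value for b, so these are assumed values at 300 per arm (SE 46.3 g):

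| b (g) | b/SE | Two tails | False-positive rate |
|---|---|---|---|
| 0 | 0 | 0.0250 + 0.0250 | 5.0% |
| 12 | 0.259 | 0.0445 + 0.0132 | 5.8% |
| 26 (one fifth of 130) | 0.562 | 0.0810 + 0.0058 | 8.7% |
| 39 (three tenths of 130) | 0.842 | 0.1319 + 0.0025 | 13.4% |

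For gestational length (SE = 9 × √(2/300) = 0.735 days), an assumed 0.525 days, a quarter of 2.1, gives about 11%. Recruiting more women does not remove such a bias.

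**Does unequal acceptance break the sample size?**

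Take 600 eligible women per period (Design) and 300 in the intervention arm. Assumed acceptance of 40%, 30% or 25% among controls gives 240, 180 or 150 women. Detectable difference = 2.802 × 567 × √(1/300 + 1/n of controls) = 138, 150 or 159 g. In the worst case SE = 567 × √(1/300 + 1/150) = 56.7 g, the same as Table 1's column for 400 participants.

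**The case against.** The study does not hide that it is non-randomised, and several mitigations are real: one examiner, fixed numeric criteria in both periods, seven covariates, and primary outcomes that the dentist does not assess. These stand, and they limit the concern. They do not reach selection at acceptance or an examiner's drift at the threshold.

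A reader might infer more than the article supports:

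- **That women are told their arm before consent.** Design says only that they are informed about the study. The invitation and consent texts are not shown, and a common text may already be in use.
- **That the pilot shows the two offers attract different women.** Patient and public involvement names cost and low priority as barriers to dental visits. If treatment is free in both arms, the cost barrier falls in both. The pilot women were also willing to take part. About half of recruited women are expected to have no periodontitis, so at acceptance the timing of treatment is only a conditional part of the offer.
- **That composition would shift by a known amount.** Suppose regular attenders accept deferral at 30% and others at 50%. Design's 65/35 split then gives 0.35 × 0.5 / (0.65 × 0.3 + 0.35 × 0.5) = 47% non-regular attenders among controls, against 35%. This needs equal periodontitis prevalence in both groups, and Design says prevalence in non-attenders is unknown. The direction is also arbitrary. Even granting it, the 12.3-point shift yields 26 g only if attendance is worth about 211 g (26/0.123), and 39 g only at about 317 g, after adjustment. At 100 g it yields about 12 g.
- **That lower acceptance undermines the power calculation.** The 50% is stated as a condition, and even 25% among controls stays within Table 1's second column. That column is meant for dropout and missing data, so only both losses together would exceed it.

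**Conclusion.** The point holds as a risk of selection by arm that the planned analysis does not address as well as it could. Assignment by period is stated. Predictability to staff and dentist follows from it, and knowledge on the woman's side is an inference. The article shows neither that selection differs by arm nor how much it would matter. The false-positive rates of 5.8% to 13.4% rest entirely on assumed residual differences of 12 to 39 g at 300 per arm. They show sensitivity and are not estimates. Sample size is not the issue. What can be corrected now is the adjustment list, the definition of the analysis set, and the reporting of how women entered each arm.

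**What to change.** 1. Add baseline dental attendance and baseline periodontal severity (stage, or mean attachment loss and pocket depth) to the primary regression of gestational length and birth weight.
2. Define the primary analysis set as every consented, screened woman diagnosed stage I–III, whether or not she takes up treatment. Statistics already includes participants regardless of adherence; this fixes the point from which that applies.
3. Report invited, accepting, screened and diagnosed numbers, and the stage distribution, by period. State that residual selection by arm limits causal conclusions.
4. Only where it can still be identical in both periods, use one invitation text and lock staging in REDCap before treatment timing is discussed. Introduced partway, it would itself make the invitation differ by arm. Disclosing timing later also needs ethics review.

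**Cost.** Items 1 to 3 need two more covariates, drawn from data the article says are collected, and some counting. Item 2 dilutes the effect slightly through diagnosed women who decline treatment. If recruitment is over, it is possible only as far as data on those women were kept.

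**Limits.** None of this blinds the dentist to period. If measurement itself drifts between periods, adjusting for measured severity carries that drift along. Calendar-time confounding remains. Individual randomisation after diagnosis would remove the problem, but it is a redesign of a study declared non-randomised.

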**Fig 1 pone.0302010.g001:**
[figure not shown]
SPIRIT schedule of enrollment, screening, and interventions.

Demographic information, data related to mental health, use of medicine, diet intake, smoking status, physical activity, socioeconomic status, oral health care and dental habits will be collected at baseline (gestational week 11–13) and at gestational week 35 via online questionnaires. Two months and six months post-partum additional questionnaires addressing the birth information, growth of the baby, breastfeeding, educational and employment status of the partner, weight and height of the partner, current weight of the mother, oral health and dental habits of the mother, and level of contentment for participating in the study will be sent online to all enrolled participants (S1 Appendix).

Dental treatment takes place at regional dental clinics in Holbaek, Kalundborg, Vordingborg and Maribo, all in Region Zealand, close to the participants residence, in order to facilitate a potential implementation of the project afterwards in the antennal care program.

### Patient and public involvement

A small pilot study was initially conducted in the planning phase of the study and included vulnerable pregnant women. The included pregnant women, who did not see a dentist regularly (defined as no dental visits within the last 18 months and/or 2 or less dental visits within the last 5 years) informed that they would be willing to participate in a study like the PROBE study and believed that oral health should be given more attention during pregnancy and be implemented in the antennal care program. Another finding was that the two primary barriers for why these pregnant women in region Zealand do not see a dentist on a regular basis were economic constraints and a general lack of priority of going for regular dental visits.

Offering free dental care during pregnancy in Denmark may be an easy implementable strategy to reduce the burden of adverse birth outcomes. There will be economic expenses related to providing free dental care, but the long-term beneficial effects both for the women and children are potentially significant, and a cost effectiveness analysis is scheduled to be performed based on our results to further support this. After the PROBE intervention study has been completed a fourth and final questionnaire will be sent to all the included participants with questions addressing the participants perspectives and opinions on participating in the study.

### Outcome measures

Primary outcome measures include gestational length (days) and birth weight (g). Preterm birth is defined as birth before gestational week 37 and rates will be described below gestational week 37 and 34. Secondary outcomes include risk markers for preeclampsia (defined as hypertension and/or proteinuria) and gestational diabetes (defined as glucose intolerance).

Long term outcome measures include growth development, infections, use of medicine and hospitalizations. These measures will be collected and retrieved through the general practitioner and from medical journals until the age of 2 years.

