### Power calculation

Statistical power was evaluated prior to commencement of the study using a two-sample means test. Minimal detectible effects for key study outcomes; gestational length (days) and birth weight (g) at 80% power and a significance level at 0.05, assuming 600 (number of enrolled) or 400 participants (200 participants with dropout and/or missing information), are presented below (Table 1).

**Table 1 pone.0302010.t001:** Power calculation.

Outcomes	Expected mean (SD)	Minimal detectable effect (n = 600)	Minimal detectable effect (n = 400)
Gestational length (days)	272 (9)	2.1	2.5
Birth Weight (g)	3490 (567)	130	159

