### Statistics

Baseline characteristics of participants will be summarized using descriptive statistics (i.e. means and standard deviations for normally distributed continuous variables, medians and ranges for skewed continuous variables, frequencies and proportions for categorical/binary variables), for both treatment arms and for the total sample. All analyses will be conducted according to the intention-to-treat approach, including all participants, regardless of adherence to the study protocol. The effect of the periodontal treatment performed during pregnancy will be analyzed with regression analyses adjusted for relevant confounders (age, BMI, parity, smoking status, medicine use, socioeconomic status and education level). In addition, statistical analyses (multiple regression analysis, potentially spline analysis) of the changes in hormonal and inflammatory markers in both treatment arms will be performed. To determine the effects of the intervention, time and group-time interaction on outcomes (inflammatory and hormonal markers, glycemic control and periodontitis status), one-way repeated measures ANOVA will be applied. Procedure for testing an interaction effect: If the interaction effect is significant, provide an interpretation of the results, but do not test main effects because the tests for main effects are uninteresting in light of significant interactions. If interaction effects are non-significant, drop the interaction effects from the model and test the main effects. Determining which results to present when testing interactions is often a multi-step process. Statistical software (SPSS, (version 19, Chicago IBM) will be used. A P-value < 0.05 will be considered statistically significant.

All data will be stored in password-controlled databases, and all data will be encrypted. All data collected will be anonymized using a unique study ID. Any identifiable data (e.g. consent forms) will be stored in secure, locked facilities with access limited to the study team.

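### Two primary outcomes, each sized and judged at 0.05, with no rule for what counts as primary success

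*Protocol article*

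**What the plan says.** Three sections of the protocol article bear on this.

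- Outcome measures: "Primary outcome measures include gestational length (days) and birth weight (g"). Two outcomes carry primary status, and neither is ranked above the other.
- Power calculation: "Minimal detectible effects for key study outcomes; gestational length (days) and birth weight (g) at 80% power and a significance level at 0.05". Table 1 then gives a separate row for each outcome.
- Statistics: "A P-value < 0.05 will be considered statistically significant". This is the only decision threshold in the article.

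The Statistics section does set out a stepwise procedure, but for the group-by-time interaction in the marker analyses and not for the two primaries. The Introduction describes a positive study in open terms, as findings that "show an effect of periodontal treatment on the risk of pregnancy and birth related outcomes". It does not tie that result to one primary outcome or to both.

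**The concern.** With two primaries and a common threshold of 0.05, what the study may claim depends on a rule that is not given. If either outcome can carry the claim, there are two chances of a false positive and the overall error exceeds 5%. If both must succeed, the error is controlled but the 80% behind Table 1 is not the power for success. Left open, the headline outcome can be chosen after the results are known. That matters here because the Introduction links a positive finding to a public message about giving dental treatment in pregnancy higher priority.

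This goes somewhat beyond a detail left to a statistical analysis plan. The article itself fixes 0.05 for each primary, both in the sizing and in the analysis threshold.

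**Working it through.** **Inputs.** From Table 1: SD 9 days for gestational length and 567 g for birth weight. From Power calculation: "Statistical power was evaluated prior to commencement of the study using a two-sample means test", 80% power, alpha 0.05, and "assuming 600 (number of enrolled) or 400 participants (200 participants with dropout and/or missing information"). From Design: "we can include 300 women in each of the two study arms", so 300 per arm, or 200 per arm after loss. Sidedness is not stated; two-sided reproduces the table. The correlation between the two test statistics is not given, so it is assumed and varied from 0 to 0.9.

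**Step 1: reproduce Table 1.** MDE = (z₀.₉₇₅ + z₀.₈₀) × SD × √(2/n per arm), with 1.960 + 0.842 = 2.802.

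| Outcome | n per arm | Calculation | Result | Table 1 |
|---|---|---|---|---|
| Gestational length | 300 | 2.802 × 9 × √(2/300) | 2.06 days | 2.1 |
| Gestational length | 200 | 2.802 × 9 × √(2/200) | 2.52 days | 2.5 |
| Birth weight | 300 | 2.802 × 567 × √(2/300) | 129.7 g | 130 |
| Birth weight | 200 | 2.802 × 567 × √(2/200) | 158.8 g | 159 |

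The table is right for each outcome at its stated alpha.

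**Step 2: error and power under the two open readings.** For independent tests, the chance of at least one false positive is 1 − 0.95² = 9.75%. For correlated tests it comes from the bivariate normal distribution with limits ±1.960. The benefit-direction column counts only false findings of benefit; a single test has 2.5%. Joint power is the chance that both tests are significant when each alone has 80% power.

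| Correlation (assumed) | Either suffices: false positive, two-sided | Either suffices: benefit direction only | Both required: joint power |
|---|---|---|---|
| 0 | 9.8% | 4.9% | 64% |
| 0.6 | 8.8% | 4.4% | 70% |
| 0.8 | 7.8% | 3.9% | 73% |
| 0.9 | 7.0% | 3.5% | 75% |

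**Step 3: the cost of splitting alpha.** At 0.025 per outcome the multiplier is z₀.₉₈₇₅ + z₀.₈₀ = 2.241 + 0.842 = 3.083. Detectable effects grow by 3.083/2.802, about 10%.

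| Outcome | n = 600 | n = 400 |
|---|---|---|
| Gestational length | 2.27 days | 2.77 days |
| Birth weight | 143 g | 175 g |

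These are Bonferroni figures. At the effects printed in Table 1, Bonferroni power per outcome is 73% and 70% for gestational length (n = 600 and 400) and 71% at both sizes for birth weight.

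Holm does better, because once one outcome passes at 0.025 the other is tested at 0.05. If both effects are real and each alone has 80% power at 0.05, Holm's power per outcome is about 78% at correlation 0 and 75% at 0.9. If only one effect is real, it is about the Bonferroni 70-73% or slightly more. The power to succeed on at least one outcome at 0.025 each, with both effects real, is 92% at correlation 0, 84% at 0.6, 80% at 0.8 and 77% at 0.9.

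**The case against.** The strongest case on the other side has four parts.

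- **It is an omission.** A multiplicity rule is often placed in the statistical analysis plan, and this is a condensed article. That stands in part: an unseen plan may hold a rule. But the article fixes 0.05 twice for two primaries. A plan that split alpha would depart from the level used for Table 1, and one that required both outcomes would make 80% the wrong figure for success.
- **No either-or claim is made.** A reader might infer that the false-claim rate of this study simply is 8-10%. The documents do not support that. The article permits an either-or claim but does not state one, the two-sided rate counts false findings of harm, and the rate drops below 8% once the correlation passes about 0.77. This part stands in full, so every rate here is conditional.
- **Table 1 is not wrong.** A reader might infer that it was computed at the wrong level, or that controlling the error brings power down to 70-73%. Neither follows. The table gives detectable effects for each outcome and reproduces at 0.05. The 70-73% is Bonferroni power for one outcome alone; Holm loses less when both effects are real, and for an either-or claim the matching quantity is the power for at least one success, 77-92%.
- **Chance error is not the main threat.** The control group is recruited in a further 18 months and the design is non-randomised, so confounding may matter more. That is fair, and it limits the practical weight of the point, but it does not justify leaving the claim undefined.

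**Conclusion.** The point holds in a conditional form. The protocol article names two primaries, sizes and judges each at 0.05, and does not say what combination of results is a success.

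Under either open reading something is off. If either outcome suffices, the two-sided chance of at least one false positive is about 7-10%; in the benefit direction it is about 3.5-4.9% against 2.5%. If both are required, there is no inflation, but joint power at the Table 1 effects is about 64-75%. Only a stated order or a single primary would leave a Table 1 row as it is, and the article gives neither.

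The figures rest on an assumed correlation, two-sided tests, equal arms and the unadjusted two-sample comparison behind Table 1. The planned regressions adjust for covariates, so they are approximate. The absence of a rule is certain from the text; the size of its effect is not. This is a cheap improvement that should be made, and it does not invalidate the study.

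**What to change.** Before outcome data are seen, state one rule for the two primary outcomes. Either of these will do:

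- **Holm across gestational length and birth weight.** Add to Table 1 the conservative detectable effects at 0.025: 2.3 days and 143 g for n = 600, and 2.8 days and 175 g for n = 400. Label them as Bonferroni figures. Note that Holm's power per outcome at the Table 1 effects is about 75-78% if both effects are real, and about 70-73% or slightly more if only one is. The cost is this modest loss of power per outcome.
- **A fixed sequence, each test at 0.05.** The second outcome is tested only if the first is significant. The documents give no basis for ranking the two, so the order is the sponsor's choice. The Table 1 row for the first outcome stays as it is. The cost is that the second outcome alone cannot support a confirmatory claim.

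Report both estimates with confidence intervals whichever rule is chosen. The text change is one sentence, plus the added figures under Holm. Neither rule addresses confounding, which needs its own treatment in this non-randomised design.
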